### Overall study design

This is a randomized community-field trial including five GDM screening strategies in a parallel group design. Recruitment of the participants took place between September 2016 and January 2019 in 1015 health centers in 25 selected cities of five provinces of Iran.

All pregnant women < 14 weeks of gestation, who received prenatal care from governmental health care systems were eligible for enrollment, except where the following specific exclusion criteria prevented this: Maternal age < 18 years, preexisting diabetes, date of last menstrual period not certain, no ultrasound estimation from 6 to 14 weeks of gestational age available, chronic hypertension, asthma or currently receiving treatment with oral glucocorticoids, β-blockers, oral β-mimetics, Dilantin, or antiretroviral agents and past history of bariatric surgery.

All participants received standard prenatal care recommended by the American College of Obstetricians and Gynecologists (ACOG) [41]. Moreover, participants were scheduled to have two phases of GDM screening in the first and second trimesters of pregnancy, based on the pre-specified protocol for GDM screening, selected for each city.

At each prenatal visit, standardized questionnaires were administered to document prenatal as well as other data needed for research by trained midwives.

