### Randomization and allocation

Initially all provinces of Iran were categorized to five stratum based on their geographic location (North, East, West, South, and Center of Iran) and one province in each stratum were randomly selected; then, the list of the cities located in each province were provided. Since the socioeconomic status in the center of provinces may differ from other cities, in the second phase, all cities in each province were classified in two clusters of center of the province and other cities. At the end, four cities were randomly selected from the list of other cities in each province.

For allocation of protocols, in the cluster of the provincial centers, five different protocols were randomly allocated to each provincial center. Also, in the cluster of other cities, four other cities in each province were randomly allocated to the rest of the protocols (Fig. 1). Sample size for each city was estimated through probability proportional to size (PPS), defined by number of live births of the cities.

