### Intervention

Following the approval of this study, the study procedure was released as a guideline to all the selected cities. In this respect, workshops were conducted in each city to introduce the study protocol and train the caregivers and study staff accordingly. Dieticians, obstetricians, internal medics, laboratory technicians and endocrinologists in each province were invited to a scientific workshop to harmonize and coordinate the follow ups and treatment of GDM patients. Scientific teams with specialists and executive members conducted visits every 2 months. A telegram channel was developed for daily online communication of scientific members and executive members at both provincial and city levels to answer questions and solve any problems encountered.

Along with routine standard prenatal care, all pregnant women was screened for GDM based on the pre-specified protocol assigned to each city. In this respect, early screening of GDM was conducted in the first trimester of pregnancy, using fasting plasma glucose (FPG) from venous sample with the specific threshold based on each screening protocol; based on the results of those screening tests, pregnant women were classified in to three groups: (i) diagnosed with preexisting pre-gestational overt diabetes; (ii) gestational diabetes and (iii) non-GDM women. In addition, at 24–28 weeks of gestation, those not previously known to have diabetes (overt or gestational), were screened again for GDM based on pre-specified protocol criteria assigned to that city. All study participants were followed till delivery and pregnancy and neonatal outcomes and health cost were recorded in detail. Definitions of various protocols for screening are presented in Table 1.

**Table 1 Tab1:** Definitions of various protocols for screening of gestational diabetes mellitus

Protocol	First trimester	Second trimester		
	Diagnostic criteria for GDM	Method for GDM screening	Diagnostic threshold of test	Diagnostic criteria
A	92 mg/dL < FPG > 126 mg/dL	One step with 2-h 75 g OGTT	Fasting ≥ 92 mg/dL 1 h ≥ 180 mg/dL 2 h ≥ 153 mg/dL	GDM is defined as any of the given plasma glucose values are met or exceeded
B	100 mg/dL < FPG > 126 mg/dL	One step with 2-h 75 g OGTT	Fasting ≥ 92 mg/dL 1 h ≥ 180 mg/dL 2 h ≥ 153 mg/dL	GDM is defined as two or more of the given plasma glucose values are met or exceeded

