### Data collection

Data were collected from participants at scheduled time points (Table 2) using pre-specified questionnaires and clinical and para clinical exams by trained midwives. Moreover, data on neonatal mortalities that occurred after hospital discharge were collected at 4 weeks post-partum by telephone and subsequent reviews of medical records.

**Table 2 Tab2:** Outlines of periodic assessments of study participants

	Method or sample used	> 14 week	14–19 week	20–23 week	24–30 week	31–34 week	35–37 week	38 week	39 week	40 week	Birth	28 days after birth
Maternal^a,b^												
Past medical, reproductive and obstetrics history												
Weight	Calibrated scale	^a^	^a^	^a^	^a^	^a^	^a^	^a^	^a^	^a^		
Height	Stadiometer	^a^										
Blood pressure (systolic, diastolic)	Calibrated mercury sphygmomanometer	^a^	^a^	^a^	^a^	^a^	^a^	^a^	^a^	^a^		
Fundal height	Measuring tape		^a^	^a^	^a^	^a^	^a^	^a^	^a^	^a^		
Fetal heart rate			^a^	^a^	^a^	^a^	^a^	^a^	^a^	^a^		
Fetal ultrasound		^a^			^a^		^a^					
FPG	Venous sample	^a^										
OGTT-75 g or GCT following OGTT-100 g	Venous sample				^a^							
Quality of life	Questionnaire		^a^	^a^	^a^	^a^		^a^				
Drug adherence	Questionnaire		^a^	^a^	^a^	^a^		^a^				
GDM treatment satisfaction	Questionnaire		^a^	^a^	^a^	^a^		^a^				
Cost-effectiveness	Questionnaire		^a^	^a^	^a^	^a^		^a^			^a^	
Feto-maternal outcomes^c^											^a^	
Neonatal^a,b^												
C-peptide	Cord sample										^a^	
Weight	Calibrated baby scale										^a^	
Recumbent length	Infantometer										^a^	
Head circumference	Measuring tape										^a^	
Blood glucose^e^	Heel-stick sample										^a^	
Neonatal outcomes^d^											^a^	^a^

^a^Data collected from routine and expert scans that occur during the time points

^b^If GDM or other complication were diagnosed, subsequent additional visits, measurements and standard treatment were performed

^c^Feto-maternal outcomes continuously recoded include abortion, gestational hypertension, pre-eclampsia/eclampsia, preterm birth, instrumental delivery, primary cesarean section, polyhydramnios, oligohydramnios, premature rupture of membrane, placenta Previa, placenta abruption, postpartum hemorrhage, wound and incision infection

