### Questionnaires

*Prenatal questionnaire* This comprehensive questionnaire includes two sections: 1—contains the past medical, reproductive, obstetrics, and gynecological history, completed only at first prenatal visit 2—focuses on current pregnancy information and this part was completed at each prenatal visit during pregnancy (Additional file 1: PART 1: Prenatal Care Form).*Delivery, postpartum and neonatal questionnaire* This questionnaire contains the details of delivery and its methods and any adverse maternal–fetal/neonatal outcomes (Additional file 1: PART 2. Childbirth and New-born Report Form).*Quality of life questionnaire* The Iranian version of 36-item short form health survey questionnaire (SF-36) [45–48] was used to measure the physical and mental components of health-related quality of life. The SF-36 included 36 items with 8 subscales; physical functioning, role limitations due to physical problems, bodily pain, general health perceptions, vitality, social functioning, role limitations due to emotional problems and perceived mental health. This questionnaire was completed monthly for all GDM patients since the time of diagnosis. Also, it were done for 5% of non-GDM pregnant women visited from the first visit for prenatal care (Additional file 1: PART 3. 36-Item Short Form Survey Instrument).*Cost-effectiveness questionnaire* This questionnaire included 50 items with three subscales: (i) self-purchased health care, (ii) travel costs for making return visit(s) to health care and (iii) time costs of travelling and attending health care center. Effectiveness was measured in terms of quality adjusted life years (QALYs), using the EQ-5D 3L questionnaire completed by participants at the follow up time points. It includes five questions, each assessing one of five dimensions of the health related quality of life (Mobility, Self-Care, Usual Activities, Pain/Discomfort and Anxiety/Depression). Each of these dimensions has to be answered on a 3-level scale (no problems, some or moderate problems, and extreme problems). The scales are scored from 1 (no problem) to 3 (extreme problem) in each question; and finally the score digits are placed together to yield a 5-digit code for the health status of each patient (Additional file 1: PART 4. Cost effectiveness Form).

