### Cost-effectiveness analysis (CEA)

A cost-effectiveness analysis, comparing 4 less intensive screening strategies with IADPSG criteria will be conducted on an intention-to-treat basis by estimating various parameters including Quality-adjusted life years (QALYs), incremental cost-effectiveness ratio (ICER), and incremental net benefit (INB). To estimate mean cost in each treatment group, regression models will be used. General linear models (GLM) with appropriate variance functions e.g. gamma, Poisson, etc. and link will be used to identify the relationship between treatment allocation and costs after adjusting for minimization and the appropriate prognostic covariates at baseline (e.g. Baseline EQ-5D score). To estimate the incremental effect of the treatment indicator variable, recycled predictions will be used [64].

A sensitivity analysis will be conducted to assess how sensitive the cost-effectiveness results are to variation in key parameters including cost.

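### The cost model adjusts for a minimisation the trial did not use and, on the published schedule, for a baseline EQ-5D first collected after arm-specific first-trimester classification

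*Protocol article*

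**What the plan says.** The section on cost-effectiveness analysis fits a regression of cost on allocated protocol "after adjusting for minimization and the appropriate prognostic covariates at baseline (e.g. Baseline EQ-5D score", and then obtains the incremental effect by recycled predictions.

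The section on randomization and allocation describes how protocols reached cities. For the provincial capitals, "in the cluster of the provincial centers, five different protocols were randomly allocated to each provincial center". For the remainder, "four other cities in each province were randomly allocated to the rest of the protocols".

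On timing, the Overall study design section says "All pregnant women < 14 weeks of gestation, who received prenatal care from governmental health care systems were eligible for enrollment", and the Intervention section says "early screening of GDM was conducted in the first trimester of pregnancy, using fasting plasma glucose (FPG", with women sorted on that result into overt diabetes, GDM or non-GDM. Table 1 sets the lower first-trimester limit for GDM at 92 mg/dL in protocols A and D and at 100 mg/dL in B, C and E.

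The Questionnaires section places the EQ-5D-3L within the cost-effectiveness questionnaire and has QALYs measured "using the EQ-5D 3L questionnaire completed by participants at the follow up time points". Table 2, titled "Outlines of periodic assessments of study participants", leaves the cost-effectiveness row empty in its first column and marks it from 14–19 weeks onward. Fasting glucose is marked in the first column only.

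**The concern.** An adjustment set should list the factors that shaped the allocation and variables that the allocation could not have changed. The stated set appears to fail on both counts.

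First, adjusting for minimisation normally means including the minimisation factors. If there were none, the instruction cannot be carried out, and an analyst would have to guess what was meant. The factors that did structure the allocation are not named in that paragraph.

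Second, a score taken after women have been screened under their city's protocol is not a baseline. A woman with a fasting value between 92 and 100 mg/dL is told she has GDM, and starts management, in A or D; in B, C or E she is not. The Background section itself says that over-diagnosis may cause stress and impair quality of life. If the label moves EQ-5D, and EQ-5D is related to cost, adjustment for EQ-5D takes out part of the cost difference that the model is meant to estimate. Comparing the cost-effectiveness of the protocols is a stated aim, and cost is one of the listed hypotheses.

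**Working it through.** There is no planned figure to reproduce. The check sets the sections side by side.

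**Allocation.**
- Five provinces were drawn, one per geographic stratum. Each contributes its centre and four other cities: 5 × (1 + 4) = 25, which matches the 25 cities in the Overall study design section.
- I read the allocation as one distinct protocol per centre, with the remaining four protocols spread over that province's other four cities. Each province then holds every protocol once, and each protocol has one centre and four other cities.
- This is a complete description of a restricted randomisation. It leaves no step at which minimisation could enter, and the term occurs only in the cost-effectiveness section. The design factors are province, and provincial centre versus other city.

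**Timing of EQ-5D against first classification.**
1. Enrolment is before 14 weeks. Table 2's first column is printed as > 14 weeks and must mean < 14.
2. Fasting glucose is taken in that column, and classification at the arm's threshold follows.
3. The questionnaire carrying EQ-5D is first marked one column later, at 14–19 weeks.
4. The text of the Questionnaires section agrees: it speaks of follow-up time points and mentions no enrolment measurement.
5. The second-trimester test is at 24–28 weeks, after the first scheduled EQ-5D.

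The first scheduled EQ-5D is therefore post-allocation. For women diagnosed in the first trimester it is also post-diagnosis.

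**Which contrasts are exposed.** The reference is A. Early lower limits, in mg/dL:

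| Contrast | A | Comparator | Early labelling differs? |
|---|---|---|---|
| A vs B | 92 | 100 | yes |
| A vs C | 92 | 100 | yes |
| A vs D | 92 | 92 | no |
| A vs E | 92 | 100 | yes |

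A and C share the same second-trimester test and criteria, so the early threshold is the whole difference between them. That makes A versus C the most exposed contrast.

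**Direction and size.** On a linear scale the total arm effect on cost is τ = τ′ + αβ. Here α is the effect of arm on the 14–19-week EQ-5D, β is the effect of that EQ-5D on cost given arm, and τ′ is what remains after adjustment. To a first approximation α = q × d, where q is the share of women with first-trimester values between 92 and 100 mg/dL and d is the mean shift in EQ-5D caused by label and management. With no other common causes of EQ-5D and cost, adjustment removes q × d × β. The document gives none of q, d or β, so no number can be attached. If unmeasured factors, such as early pregnancy complications, drive both EQ-5D and cost, conditioning can also bias τ′ in either direction. Recycled predictions do not restore the lost part: they hold the EQ-5D values fixed while switching the arm.

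**The case against.** The case against the EQ-5D part has weight.

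- **Blanks in Table 2 are unreliable.** The row for past history is empty throughout, although the prenatal questionnaire collects it at the first visit. The quality-of-life row is empty in the first column, although the SF-36 was given to a sample of non-GDM women from that visit. An empty cell does not prove that no first-visit EQ-5D exists. This stands as a caution. The other rows are nevertheless plausibly aligned (height only in the first column, fundal height and fetal heart rate from 14–19 weeks), and the running text on EQ-5D points the same way independently of the table.
- **EQ-5D is given only as an example covariate, and in the cost model.** Also true. It is, however, the only covariate named, and the point is confined here to costs.
- **Only early diagnoses precede the score.** Accepted; it limits the contrasts affected, as the table shows.
- **The minimisation wording is a small slip with no demonstrated effect on a result.** Accepted as to size. It is still a statement that cannot be executed as written.

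A reader might go further and infer that the QALYs rest on a sample overloaded with GDM women, because the SF-36 went to all GDM patients while "it were done for 5% of non-GDM pregnant women visited from the first visit for prenatal care". The document does not support that. The sampling rule is stated for the SF-36; QALYs come from the EQ-5D, for which no subsample is given. Unweighted pooling is nowhere planned, and weighting may be left to the full protocol or analysis plan. A fixed weight of 20 would not follow either, since some sampled non-GDM women become GDM at 24–28 weeks.

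**Conclusion.** The adjustment set for the cost model is wrong in one part and, on the published schedule, unsuitable in the other.

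That no minimisation was used is certain from the document. This is an error of wording and no evidence that the randomisation was carried out differently from its description.

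That the only scheduled EQ-5D available as a baseline follows arm-specific classification is the natural reading of the Questionnaires section and Table 2 together. It rests on Table 2 being correctly aligned and on there being no unreported first-visit measurement. If so, adjustment may remove part of the early-labelling effect on cost for A versus B, C and E. It has no such effect through early labelling for A versus D, or through diagnoses made at 24–28 weeks. The amount is unknown.

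The clinical primary outcomes, birth weight above the 90th percentile and primary caesarean section, are not touched. Nor do the documents show bias in the QALY estimates, because the stated adjustment belongs to the cost regression. The correction should be made, but it is a modest one.

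**What to change.** 1. Replace the reference to minimisation with the design factors used: province, and provincial centre versus other city.
2. Restrict the remaining covariates to those fixed before the fasting glucose result, for example age, BMI and parity. Age and obstetric history belong to enrolment, and Table 2 marks weight and height in the first column.
3. State when the baseline EQ-5D was taken. If a pre-screening score exists, keep it as a covariate. If not, drop it from the adjustment set and treat the 14–19-week score as an outcome.

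The cost is a few lines of text, with no new data. There are two statistical prices. Losing EQ-5D as a predictor may widen the intervals for cost differences somewhat. Adding the design factors also uses city-level degrees of freedom: with 25 cities and five protocols, 25 − 1 − 4 = 20 remain without them, and 20 − 4 (province) − 1 (centre) = 15 with them. That is affordable, and it reflects the randomisation as it was done.

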### Bayesian and Markov Modeling

Bayesian Cost Effectiveness Modeling (BCEM) will be used to overcome the complexity of the relationships linking a suitable measure of clinical benefit (e.g. quality-adjusted life years) and the associated costs. Simplifying assumptions, such as normality of the underlying distributions, are usually not granted, particularly for the cost variable, which is significantly skewed distributions. In addition, individual-level data sets are often characterized by the presence of structural zeros in the cost variable [65–67]. Bayesian models will be used to account for the presence of excess zeros in a distribution and have been applied in the context of cost data (Fig. 3).

**Fig. 3 Fig3:**
[figure not shown]
A schematic illustration of the process of health economic evaluation

Markov model will be used to extrapolate the results of the trial beyond the follow up, which will eventually provide longer-term cost-effectiveness. Markov decision processes (MDPs) are a powerful and appropriate technique for modelling medical decision. MDPs are most useful in classes of problems involving complex, stochastic and dynamic decisions like medical treatment decisions, for which they can find optimal solutions [68]. Physicians will always need to make subjective judgments about treatment strategies, but mathematical decision models can provide insight into the nature of optimal choices and guide treatment decisions [69]. Markov models can be used to describe various health states in a population of interest, and to detect the effects of various policies or therapeutic choices. In addition, we will apply decision tree analysis and then apply probabilistic approach.

All data analysis will be conducted using R (Version 2.2.2) and TreeAge (Version 13) softwares.

### Approval and ethical considerations

This trial has been approved and funded by the National Institute for Medical Research Development under Grant Agreement No IR.NIMAD.REC.1394.013. Funding source had no involvement in the study. The protocol was approved by the national ethics committee of the National Institute for Medical Research Development (Approval number: IR.NIMAD.REC.1394.013). In addition, the Iranian Ministry of Health and Medical Education (MoHME) approved the study protocol and pre specified GDM modalities were made available to all those provinces as mandatory guidelines. This field trial has been registered in Iranian Registry of Clinical Trials (Trial Registration: IRCT138707081281N1).

## Discussion

At present, there is a lack of international consensus about the diagnosis of gestational diabetes. Screening strategies, testing methods and even diagnostic optimum glycemic thresholds for GDM remain the subject of considerable debate. Although gestational diabetes mellitus is a recognized marker for an increased risk of subsequent diabetes, its clinical significance with respect to its various definitions and various adverse pregnancy outcomes has not been clearly elucidated. Women with severe gestational diabetes and highly elevated fasting plasma glucose levels apparently are at an increased risk for adverse pregnancy outcomes if treatment is not provided, yet the association of milder forms of gestational diabetes with such outcomes remains unclear. Despite the HAPO study having provided valuable evidence of the association of maternal blood glucose with adverse pregnancy outcomes, it is worth noting that HAPO study was a purely observational study that conducted in western countries.

Considering the fact that majority of births annually occur in low- and low–middle income countries with high prevalence of GDM and limited resources [5], the cost-effectivity of this definition needs to be re-evaluated in other communities; the present study will hopefully provide such information from an eastern Mediterranean region. Moreover there is little information comparing the clinical efficacy, utility and feasibility of the two step GDM screening test and a 3-h oral glucose tolerance test (GTT) and the one step oral glucose tolerance test (OGTT) approaches, our study will provide comprehensive data on this comparison in the same population.

According to a WHO report, global and local decision making regarding GDM strategies are challenging due to the lack of optimum economic evaluations of various GDM screening protocols; as a result our study will provide the data needed for each community to adopt its specific GDM screening guidelines according to the reasonable cost for prevention of the adverse short and long term effects of GDM.

The limitations of our study of course should be addressed. Since specific questionnaires for evaluation of QOL and drug adherence in patients with GDM were not available, general questionnaires was used. In addition, we did not use the central reference laboratory for all of our measurement except C-peptide. Since homogeneity of laboratory procedures are essential to the success the study, we used standardized procedures in all provinces including local training of field center laboratory personnel, using a common protocol for measurement of glucose; using of standard equipment and supplies; monthly external quality controls for each laboratory. Moreover, glycosylated hemoglobin A1c (HbA1c) measurements were not available in our study.

